## 12.2. Causality assessment

For each AE, an assessment of the relationship of the AE to the study intervention(s) will be undertaken. The relationship of the adverse event with the study procedures will be categorized as unrelated, unlikely to be related, possibly related, probably related, or definitely related. An intervention-related AE refers to an AE for which there is a possible, probable or definite relationship to the study intervention. The investigator will use clinical judgment to determine the

relationship. Alternative causes of the AE, such as the natural history of pre-existing medical conditions, concomitant therapy, other risk factors and the temporal relationship of the event to administration of ivermectin will be considered and investigated.

### **12.3. Reporting procedures for AEs (Excluding SAEs)**

All AEs occurring during the study, since the signature of the Informed Consent Form until the end of the follow up period, observed by the investigator or reported by the participant will be recorded in the CRF. Malaria events occurring at any time during the study will be recorded as an AE.

AEs that result in a participant's withdrawal from the study or that are present at the end of the study will be followed up (if participant's consent to this) until a satisfactory resolution or stabilization occurs, or until a non-study related causality is assigned.

**Grade 1** Mild: Transient or mild discomfort (< 48 hours); no medical intervention/therapy required;

**Grade 2** Moderate: Mild to moderate limitation in activity - some assistance may be needed; no or minimal medical intervention/therapy required;

**Grade 3** Severe: Marked limitation in activity, some assistance usually required; medical intervention/therapy required, hospitalization possible;

**Grade 4** Potentially life threatening: Extreme limitation in activity, significant assistance required; significant medical intervention/therapy required, hospitalization or hospice care probable.

### **12.4. Reporting procedures for SAEs**

#### **Procedures for Unblinding in case of safety issues**

If it is medically imperative to know which trial medication the participant is receiving, the investigator or authorized person should open the randomization envelop. A trial-specific SOP that describes unblinding in detail will be implemented before trial initiation.

#### **Reporting procedure to the Sponsor**

Serious Adverse Event (SAE) must be reported within 24 hours by the clinical site to the sponsor, according to sponsor guidelines.

### **12.5. Reporting Procedures for SUSARS**

Investigator will report all SUSARs to the Ethics Committee (EC) within 7 calendar days in case of Fatal and life-threatening SUSARs and within 15 calendar days in case of SUSARs that are not fatal or life threatening.

Investigator will also inform all investigators concerned of relevant information about SUSARs that could adversely affect the safety of participants.

### **12.6. Safety hold of the study and stopping rules**

The study may be placed on safety hold for the following reasons

- On advice of the safety monitor;
- On advice of the investigators;
- On advice of the EC
- One or more participants experience a SAE that is determined to be related to the study product administration;
- One or more grade 3 or higher adverse events which are unexpected and possibly or probably related to the drug administration.

If the study is placed on hold it may only be restarted following discussion with and approval from the Safety monitor, the sponsor and study investigators.

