## 4. Trial design

### 4.1. Trial overview

The study is designed as a dose escalation trial with who stapes to assess the safety and efficacy of ivermectin on the reduction of *P. falciparum* parasitaemia in asymptomatic participants in

an endemic area of Gabon. The first stage is an open label trial and included arms I-III. The next stage is a randomized double-blind controlled trial. Potential adult participants living in Lambaréné and in the Tsamba-Magotsi Department, Gabon will be screened for parasitaemia of 200 to 5000 *P. falciparum* parasites/ $\mu$ l without clinical signs of malaria for inclusion in the clinical trial. Participants will be included sequentially in arms I-IV with a pause between arms to allow safety review by DSMB. Each dose escalation stage will only commence after safety assessment of the previous stage and approval by the Data and Safety Monitoring Board. The sponsor can, in consultation with the DSMB, suspend recruitment at any time based on safety considerations.

Study arms:

- Arm I: 5 participants (200  $\mu$ g/kg single dose)
- Arm II: 5 participants (2x200  $\mu$ g/kg)
- Arm III: 5 participants (3x200  $\mu$ g/kg)
- Arm IV:
  - a) 17 participants (3x300  $\mu$ g/kg)
  - b) 17 participants (placebo-control)

All participants will be hospitalized for three days. Assessment during treatment period and follow-up visit will be the same in all study arms.

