### 6.2. Treatment

#### 6.2.1. Treatment arms

Participants fulfilling all inclusion criteria and none of the exclusion criteria will be assigned sequentially to receive ivermectin 200 µg/kg orally single dose for one (5 first subjects), two or three days (10 next available subjects). Following interim safety analysis, 34 subjects will be randomly allocated in two treatment arms to receive either 300 µg/kg per day for 3 days or placebo for 3 days. There will be four consecutive study arms (arms IV a) and b) will be parallel):

- Arm I: 5 participants (200 µg/kg single dose)
- Arm II: 5 participants (2x200 µg/kg)

- Arm III: 5 participants (3x200 µg/kg)
- Arm IV:
  - a) 17 participants (3x300 µg/kg)
  - b) 17 participants (placebo-control)

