#### 6.2.2. Randomization of treatment

As Arms I-III serves descriptive purposes for safety assessment of the study drug, there will be no randomization.

Participants for Arm IV will be randomized to arm IVa or arm IV b through a randomization system prior to the first treatment. The randomization ratio will be 1:1 (3-day treatment, control group). A dedicated member of the team, who is not involved in volunteer management or diagnostic activities, will keep the randomization envelopes and dosing schedule. A third party outside the study team and sponsor will generate and distribute the randomization list and sealed envelopes using a random number generator.

A sealed envelope containing the participants arm will be used for randomization in the study and the randomization data are kept strictly confidential until formal interim safety review or the final analysis. At the time of final analysis, the allocation data will be loaded into the statistical programming system for access to trial statisticians and pharmacokinetics.

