## 12. Safety assessment

There will be a DSMB set up to assess the safety of the different study dose regimens. Safety of ivermectin treatment will be assessed by analysing the frequency, incidence and nature of adverse events and serious adverse events arising during the study. The respective next treatment arm will only be commenced after the DSMB deems it to be safe.

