## **13. Quality control and quality assurance procedures**

A safety monitor, i.e. a clinician with experience in clinical trials who is permanently on site and is independent of the clinical trial team, will oversee participant safety.

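### Section 12.6 lets dosing restart after a safety hold without required DSMB approval, which matters most in Arm IV, where no later required DSMB review follows

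*Protocol*

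**What the plan says.** **Role of the DSMB.** Section 4.1 of the protocol states: "Participants will be included sequentially in arms I-IV with a pause between arms to allow safety review by DSMB". Section 12 repeats the condition: "The respective next treatment arm will only be commenced after the DSMB deems it to be safe". Section 4.1 also gives the DSMB a part in stopping: "The sponsor can, in consultation with the DSMB, suspend recruitment at any time based on safety considerations".

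**Restart after a hold.** Section 12.6 lists grounds on which the study may be held. They are advice from the safety monitor, the investigators or the ethics committee, a related SAE, and an unexpected adverse event of grade 3 or higher that is possibly or probably related. Once a hold is in place, "it may only be restarted following discussion with and approval from the Safety monitor, the sponsor and study investigators".

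**Who the safety monitor is.** Section 13 describes this person as "a clinician with experience in clinical trials who is permanently on site and is independent of the clinical trial team". This is one clinician, and not the DSMB.

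**Other review and reporting.** Section 6.2.1 places an interim safety analysis before Arm IV: "Following interim safety analysis, 34 subjects will be randomly allocated in two treatment arms". Section 6.2.2 says that "the randomization data are kept strictly confidential until formal interim safety review or the final analysis". Under Section 12.4 an SAE "must be reported within 24 hours by the clinical site to the sponsor", and under Section 12.5 SUSARs go to the ethics committee.

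**The concern.** The protocol requires the DSMB to clear an arm before it opens, even when nothing untoward has been seen. It does not require the DSMB to clear a restart after an event serious enough to stop the study. The board therefore has a mandatory role at the routine step and none at the step prompted by a safety signal.

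In Arms I to III the gap is partly covered, because DSMB clearance is still needed before the next arm. Arm IV has no next arm. If it is held for a drug-related event, that event belongs to the only stage at 300 µg/kg, and dosing could resume without DSMB review of it.

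A smaller wording point sits in the same section. The last hold ground names two of the three causality categories that the protocol counts as related.

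**Working it through.** The protocol gives no figure on this point to reproduce. The check sets the passages side by side and counts participants.

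**1. Is the restart list closed?** The sentence in 12.6 uses *only* and names three parties: safety monitor, sponsor and investigators. Read as written, their approval is enough. The sentence does not forbid asking the DSMB, but it does not require it.

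**2. Could the safety monitor stand for the DSMB?** No. Section 13 describes a single on-site clinician, while Section 12 sets up the DSMB as a separate board.

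**3. Does another passage require DSMB approval of a restart?**
- Sections 4.1 and 12 require DSMB clearance before the next arm. They do not address resumption within an arm.
- The suspension sentence in 4.1 has the sponsor consult the DSMB on stopping recruitment and is silent on restarting.
- The interim safety analysis in 6.2.1 comes before Arm IV, so it cannot cover an event within Arm IV.
- The interim safety review in 6.2.2 probably does refer to Arm IV, since only that arm has randomization data to protect. It has no stated timing, trigger or reviewer, and no link to a restart.
- Sections 12.4 and 12.5 send SAEs to the sponsor and SUSARs to the ethics committee. Neither sends them to the DSMB.

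None of these supplies the missing requirement.

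**4. How many participants does it concern?** Arm sizes are from Section 4.1.
- Ivermectin recipients before the last required DSMB review: 5 + 5 + 5 = 15, all at 200 µg/kg per day and none at 300 µg/kg.
- Ivermectin recipients after it: 17, all at 3x300 µg/kg.
- All planned ivermectin recipients: 15 + 17 = 32. Share treated after the last required review: 17/32 = 53%.
- All Arm IV participants, placebo included: 17 + 17 = 34 of 49, or 69%.

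**5. The causality wording.** Section 12.2 counts possible, probable and definite relationships as related, and the SUSAR definition in 12.1 uses the same three. The last ground in 12.6 names the first two only. The SAE ground in 12.6 covers any SAE determined to be related, so a definitely related SAE is included. What falls outside the literal wording is a non-serious, unexpected event of grade 3 or higher that is definitely related.

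**The case against.** The strongest reply is that an independent check on restart already exists. The safety monitor must approve, is independent of the trial team and is permanently on site, so a restart cannot go ahead against that person's objection. This stands. The safeguard is lighter than a board, but it is not absent.

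A second reply is that the DSMB does not vanish once Arm IV starts. Its remit in Section 12 covers the different dose regimens without limiting it to Arms I to III, 4.1 involves it when the sponsor suspends recruitment, and 6.2.2 foresees some interim safety review. A DSMB charter, which is not shown, may say more. This also stands, but none of these passages makes DSMB approval a condition of restart, and the list in 12.6 reads as complete.

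A third reply is that 3x300 µg/kg is not a new exposure in humans. Section 3.3 reports higher doses as well tolerated, so a hold may be unlikely. That lowers the urgency but does not change what should happen if a hold occurs.

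A reader might infer that 12.6 contradicts 4.1 and Section 12. The documents do not support that. Those sections promise DSMB clearance between arms, and no passage promises DSMB approval of a restart within an arm.

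On the causality wording, the hold list is permissive, and the investigators, the safety monitor or the ethics committee can advise a hold for any event. The practical effect of the omission is small.

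**Conclusion.** The point holds as a gap in the restart rule. Followed as written, 12.6 allows dosing in Arm IV to resume after a drug-related event with the agreement of the safety monitor, sponsor and investigators, without DSMB review and with no later required DSMB review. All 17 participants at 3x300 µg/kg are treated in that period.

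It is a low-cost improvement to participant safety. A reader might infer that dosing would resume with no independent oversight, or that the DSMB is shut out. Neither follows, because the safety monitor's approval is required and DSMB input is not barred.

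A reader might also want a probability for the risk. The protocol gives no rate for events that would trigger a hold, and a hold is discretionary even when such an event occurs. A chance of an event under an assumed rate, or a confidence bound from the 15 earlier recipients, would not measure this defect. The count of 17 is the relevant scale.

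The conclusion assumes that the restart list in 12.6 is exhaustive, as its wording indicates, and that no unseen charter overrides it. The missing causality category is a minor wording error and adds little weight.

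**What to change.** Make three short changes to Section 12.6:

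1. Add the DSMB to the parties whose approval is required before the study restarts, alongside the safety monitor, the sponsor and the investigators.
2. Add advice of the DSMB to the grounds for a hold, in line with its part in suspension under 4.1.
3. In the last hold ground, add *definitely* to the two causality categories already named, to match 12.1 and 12.2.

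The cost is a possibly slower restart while the DSMB convenes. Sample size and the schedule of assessments are unaffected.

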## **13. Quality control and quality assurance procedures**

A safety monitor, i.e. a clinician with experience in clinical trials who is permanently on site and is independent of the clinical trial team, will oversee participant safety.

## **14. Ethics**

This study will be performed in accordance with the current revision of the Declaration of Helsinki and the latest versions of the ICH guidelines for Good Clinical Practice (GCP) and guidelines for Good Clinical Laboratory Practice (GCLP).

### **14.1. Informed Consent**

Written, informed consent will be obtained from all study participants prior to inclusion, as described above. This consent may be withdrawn by the study participant at any time, without being required to provide a reason.

## **14.2. Ethics review**

This trial will be submitted for ethical review to the Institutional Review Board (Comité d’Ethique institutionel, CEI) of the Centre de Recherches Médicales de Lambaréné (CERMEL), which is registered with the Registration Office for Human Research Protections (OHRP) with the numbers: IORG0007336 / IRB00008812.

## **14.3. Participant Confidentiality**

All data will be pseudonymized. Participants’ data will be identified by a unique study number in the database. Separate confidential files containing identifiable information will be stored in secured locations. Only the Sponsor representative, investigators, the clinical monitor, and the Institutional Review Board will have access to the records.

# **15. Data handling and record keeping**

## **15.1. Data Handling**

The investigator or his designee will be the data manager with responsibility for delegating receiving, entering, cleaning, querying, analysing and storing all data that accrues from the study. All data will be recorded in case record forms. This includes safety data, laboratory data and outcome data.

## **15.2. Record Keeping**

All files and source documents will be kept confidentially in locked safety cabinets. The investigator, coinvestigators and clinical research nurses will have access to records. The investigators will permit authorized representatives of the sponsor, and the monitors to examine clinical records for the purposes of quality assurance reviews, and evaluation of the study safety and progress.

## **15.3. Source Data and Case Report Forms (CRFs)**

All protocol-required information will be collected in CRFs designed by the investigator. Source documents will be in paper form, and the data will be entered into the clinical trial software. Source documents are original documents, data, and records from which the participant’s CRF data are obtained. For this study these will include, but are not limited to; participant consent form, blood results, laboratory records and correspondence. In this study this will include, but is not limited to medical history, medication records, vital signs, physical

examination records, blood results, adverse event data and details of study interventions. All source data and participant CRFs will be stored securely.

#### **15.4. Data Protection**

The study protocol, documentation, data and all other information generated will be held in strict confidence. No information concerning the study, or the data will be released to any unauthorized third party, without prior written approval of the sponsor.

#### **15.5. Procedures for the collection, storage of biological sample**

All study research samples are labelled by a code that only the trial site can link to the participant. Samples are stored at the trial site in secure facilities with limited access. Data will be kept in password-protected computers. Only investigators or their designees will have access to the samples and data. Identified samples may be transferred to another facility for analysis if site is not able to analyse the samples for logistical reason. Data will be archived in compliance with national and international guidelines.

